### Statistical considerations

Power is difficult to calculate given that only one study has attempted to intervene in sleep in the pre or postnatal period. That intervention was delivered early in the postpartum period. The authors found a large effect size on both sleep duration (ES = 1.15), and depressive symptoms using the Edinburgh Postnatal Depression Scale (ES= 0.78) [39]. It is unclear whether a preventative program would achieve such large effect sizes. However, studies in individuals with insomnia attending a sleep intervention have consistently found effect sizes in the 0.4 – 0.8 range [48,49]. Hence, we chose the smallest of these effect sizes in order to be conservative. This was particularly important as the effect sizes we have taken into consideration were shown in interventions that treated people for insomnia, which one would expect to have a greater effect than a preventative program wherein the sample begins at a baseline level. The effect sizes (Cohen’s d) from past sleep programs using the sleep questionnaires of the current study (the PSQI and ISI) has ranged from 0.35 – 0.88 [50]. On the basis of these in order to achieve 80% power, based on the most conservative effect size, we would need only 41 participants per group to achieve significance at 0.05 level. However, the cluster design increases the sample size requirement according to the following formula: 1 + (*m* – 1)*ICC, where ICC is the intra-cluster correlation, (the correlation between patients’ scores within each group) and *m* is the average number of patients per group. We could not find any published studies, using the sleep measures and reporting ICCs. Therefore, we based our assumptions on ICCs reported for mood variables. Again, we could not find any for EPDS, however, Adams et al. (2004) [51] published 1039 ICCs from 31 studies and found the median value to be 0.01 for the HADS (interquartile range [IQR] 0 to 0.032, range 0 to 0.840). We aim for an average group size of 6, and to be conservative took the mean for the ICC of 0.42, requiring 2.6 times the number of participants. Therefore to ensure sufficient power to find differences on quality of life at an effect size of at least 0.4, we need 107 participants per group (n=214).

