We anticipate that the support from the Royal Prince Alfred Hospital as well as the Facebook page that has been set up to accept anyone who expresses interest, will enable us to recruit a sample of 214 participants over 1.5years. We have aimed to be strategically conservative in calculating sample size.

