### Challenges

The most significant challenge that we expect to have is recruitment and the rate of attrition. We have attempted to combine the groups as closely as possible with routine prenatal care and to offer women a range of options in how to complete the questionnaires at each assessment point. In addition, to thank women for their time in participating in the study, we will offer participants the chance to win a hamper of baby goods worth $200 upon completion of their 10 month follow up questionnaires.

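### The 214 women to be enrolled equal the 214 said to be needed for 80% power, so nothing is allowed for attrition; this adds to a larger error in the base calculation

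*Protocol article*

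**What the plan says.** The sample size is set out in Statistical considerations of the protocol article. The starting number is chosen "in order to achieve 80% power, based on the most conservative effect size". The figure given for that purpose, before any adjustment for clustering, reads: "we would need only 41 participants per group to achieve significance at 0.05 level". For clustering, the authors write "We aim for an average group size of 6" and say that they "took the mean for the ICC of 0.42, requiring 2.6 times the number of participants". The result is "we need 107 participants per group (n=214", with the stated aim "to find differences on quality of life at an effect size of at least 0.4".

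The same 214 is the recruitment figure in the Abstract, the number to be randomised in Study population, and the target in Statistical considerations ("will enable us to recruit a sample of 214 participants over 1.5years"). That last paragraph also describes the sizing as deliberately conservative.

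Under Challenges the article states: "The most significant challenge that we expect to have is recruitment and the rate of attrition". Women enter in the third trimester and are assessed at 6 weeks, 4 months and 10 months after delivery. No attrition rate appears, and no step in the calculation allows for one.

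**The concern.** Both factors in the derivation are already spoken for: 41 for power and 2.6 for clustering. If the number required is also the number enrolled, each woman lost leaves fewer than the plan says it needs. The Hypotheses section names all three postnatal visits, and losses accumulate towards the last, which was timed so that most postnatal depression would have appeared. A null result there could be read as coming from a trial with 80% power when the power was lower.

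An unseen fuller document is unlikely to settle this. The article prints the whole derivation, and its product is exactly the enrolment target.

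**Working it through.** **Inputs from Statistical considerations.** Power 80%; significance level 0.05 (sidedness not stated, two-sided assumed); 41 per group before clustering; average cluster size m = 6; ICC 0.42; design effect stated as 2.6; standardised effect 0.4; published ICCs with median 0.01 and upper quartile 0.032. **Assumed, because the article gives no rate:** loss of 10%, 20% or 30%.

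**Step 1: the plan's figure.** 41 × 2.6 = 106.6, rounded up to 107 per group, and 2 × 107 = 214. The product reproduces. The only slack is the rounding, 0.4 of a woman per group.

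**Step 2: loss, taking 214 as giving exactly 80%.** The effective number per group is 107 / 2.6 = 41.15. A two-sample t-test reaches exactly 80% there at a standardised effect of about 0.625, which is used for this step only. With loss a, 107(1 − a) women per group remain. There are two cases:

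- the design effect stays at 2.6, as when whole clusters are lost;
- loss is spread within clusters, so that m = 6(1 − a) and the design effect is 1 + (m − 1) × 0.32, where 0.32 = (2.6 − 1)/5 is the ICC that 2.6 implies at m = 6.

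| Loss | Analysed per group | Effective n, 2.6 held | Power | m | Design effect | Effective n | Power |
|---|---|---|---|---|---|---|---|
| 10% | 96.3 | 37.0 | 76% | 5.4 | 2.408 | 40.0 | 79% |
| 20% | 85.6 | 32.9 | 70% | 4.8 | 2.216 | 38.6 | 77% |
| 30% | 74.9 | 28.8 | 64% | 4.2 | 2.024 | 37.0 | 76% |

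A normal approximation anchored at 41 effective women gives values within about a point of these.

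**Step 3: the base inputs.** The number per group for an effect of 0.4 is 2(1.96 + 0.842)² / 0.4² = 98.1, so about 99 (99.1 by t-test), not 41. A one-sided test would still need 78. The design effect is 1 + (6 − 1) × 0.42 = 3.1, not 2.6. Together they give 99 × 3.1 = 306.9, or 307 per group before any loss.

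**Step 4: power of 107 per group at an effect of 0.4.** The effective number is 107(1 − a) / [1 + (6(1 − a) − 1) × ICC], with loss spread within clusters:

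| ICC | No loss | 10% | 20% | 30% |
|---|---|---|---|---|
| 0.42 (adopted) | 37% | 37% | 36% | 35% |
| 0.032 (cited upper quartile) | 77% | 73% | 69% | 64% |
| 0.01 (cited median) | 81% | 77% | 72% | 67% |

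For the adopted ICC, the first cell is 107 / 3.1 = 34.5 effective women and the last is 74.9 / 2.344 = 32.0. At 20% loss the effect detectable with 80% power is 0.44 at ICC 0.01 and 0.46 at ICC 0.032. These figures count women with data at the visit; the planned mixed model recovers a little from earlier visits.

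**The case against.** The strongest objection is about cause. At the adopted ICC, power is about 37% with no loss and 35% with 30% loss. Attrition spread within clusters then costs about two points, while some 43 points are missing before anyone drops out. The falls of 13 to 14 points occur only at ICCs of 0.01 and 0.032, which the article cites and then sets aside. This stands, and it makes attrition the secondary shortfall. It does not remove the gap: correcting 41 and 2.6 would still leave no allowance for loss.

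It can also be said that the high ICC is itself a reserve. It is not, because it is already spent in the 2.6. If the cited median applied instead, the margin would be about one point (81%), gone at 10% loss.

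The article does plan against loss: two reminder emails followed by collection by phone (Data collection), a choice of completion routes and a prize draw (Challenges), and a mixed model that keeps women with partial data (Data analysis plan). These lower attrition and limit bias if data are missing at random. They do not supply a missing 10-month score, and the article still names attrition as a main challenge.

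Two stronger readings are tempting and unsupported. One is that the authors expect a particular number of women to be missing at 4 and 10 months; they give neither a rate nor a retained number. The other is that 80% is claimed specifically for depression at 10 months. The calculation is tied to no visit, draws on sleep-intervention effect sizes and names quality of life as its target, while depression is a secondary outcome.

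**Conclusion.** The point holds as a secondary shortfall. Enrolment equals the stated requirement, no loss is allowed for, and the 80% is not delivered at follow-up if any loss occurs. On the plan's own footing the cost is about 4 to 16 points for 10% to 30% loss with the design effect held at 2.6, or about 1 to 4 points if loss thins the clusters. The loss rates are assumptions, as is two-sided testing.

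A reader might infer that attrition is why the trial lacks its stated power, or that inflating 214 for dropout would restore it. The article's figures do not support either. The larger fault is the base calculation: an effect of 0.4 needs about 99 per group rather than 41, and the stated formula gives 3.1 rather than 2.6.

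**What to change.** Keep the enrolment target and rewrite the sample size paragraph in this order:

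1. Correct the base inputs: about 99 per group for an effect of 0.4, and a design effect of 3.1 for m = 6 and ICC 0.42, or a lower ICC with its justification.
2. State the range of loss assumed, and the number of women and average cluster size expected at 6 weeks, 4 months and 10 months.
3. Give power and detectable effect at each visit for those numbers.
4. Delete the statement that the sample size was chosen conservatively.

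This costs a rewritten paragraph and a short table, with no extra participants. It does mean reporting a power well below 80% unless a much lower ICC can be defended: with complete follow-up, 107 per group reaches 80% at an effect of 0.4 for the cited median ICC of 0.01 (81%) but not for 0.032 (77%).

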### Data analysis plan

There are 4 measurement time points, of which 3 are post-intervention (6 weeks, 4 month, and 10 months follow up). A linear mixed model analysis will be implemented for each factor (sleep quality and depression) at each time point. This method takes account of both fixed and random effects and is robust to account for missing data. Fixed effects will include time; (baseline, 6 week, 4 months, 10 months) and group (intervention and control). Random effects will include subjects to account for between-subject variation. Uncorrected pairwise comparisons based on estimated marginal means will evaluate the primary hypothesis of interest – that the sleep quality of the participants in the intervention group will decline less in the postpartum period than those in the control group. Comparisons of baseline measures with post treatment will be used at follow up compared with controls.

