### Hypotheses

1. Women who receive the sleep psychoeducational intervention will have better outcomes 6 weeks, 4 months and 10 months following delivery than those who do not receive the intervention on the following primary outcomes.

(a) Sleep quality – measured by the PSQI

(b) Sleep patterns – measured by shorter night wake periods indicated by the mother and infant sleep diary

(c) Self-efficacy – measured by the general self-efficacy

2. If changes in sleep, consistent with hypothesis 1(a,b) are observed, we would also expect that women who received the intervention will have fewer depressive symptoms at 6 weeks, 4 months and 10 months postpartum than the control group.

The PSQI is our primary outcome, which is a scale consisting of itemised scores which are likely to be affected differentially by pregnancy and motherhood. During pregnancy, the most common causes of disrupted sleep include the need to urinate, uncomfortable position, aching in a position, and being too hot or cold [26]. These common issues predominantly contribute to Item 5 and following the birth of the baby are generally normalised or reduced. With motherhood, women are woken several times during the night by the baby’s needs, and may develop different difficulties within Item 5. Sleep tends to deteriorate or remain unchanged for women as measured by the total PSQI. We expect this intervention will improve sleep outcomes relative to the control group.

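### The listed mixed model has no group-by-time term, so as printed it cannot test whether sleep quality declines less with the intervention

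*Protocol article*

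**What the plan says.** All the model wording is in the protocol article's Data analysis plan.

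- Fit: "A linear mixed model analysis will be implemented for each factor (sleep quality and depression) at each time point".
- Fixed effects: "Fixed effects will include time; (baseline, 6 week, 4 months, 10 months) and group (intervention and control".
- Random effects: "Random effects will include subjects to account for between-subject variation".
- Test: "Uncorrected pairwise comparisons based on estimated marginal means will evaluate the primary hypothesis of interest", that hypothesis being that "the sleep quality of the participants in the intervention group will decline less in the postpartum period than those in the control group".
- Closing sentence: "Comparisons of baseline measures with post treatment will be used at follow up compared with controls".

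Neither a group-by-time term nor a baseline covariate is named.

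Three other places bear on this. The Hypotheses section expects a benefit at each of the three postpartum visits. The Randomisation subsection has the envelope opened only after the Time 1 questionnaires are complete, so baseline precedes allocation. The Hypotheses section also describes the PSQI as made up of "itemised scores which are likely to be affected differentially by pregnancy and motherhood".

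**The concern.** A smaller decline in one arm is a between-arm difference in change over time, which is a group-by-time contrast. With additive effects of time and group, the difference between the arms' estimated marginal means is the same number at every visit, baseline included. Pairwise comparisons of those means cannot show differential change, nor a benefit that differs between 6 weeks, 4 months and 10 months.

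Two errors in the estimate follow. The single group coefficient averages in a visit at which the expected difference is zero, so a real benefit is understated. And a chance baseline difference that merely persists is reported as a group effect.

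The wording also leaves the primary model open. The possible readings have different estimands and different power, so the choice among them could be made after the data are seen.

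**Working it through.** **Inputs.** From Statistical considerations: effect size 0.4 and 107 participants per arm, taken as stated; whether 107 is the right number is a separate matter. From the Data analysis plan: four visits, three of them postpartum. Assumed, because the documents do not say: complete data, SD 1 at each visit, equal correlation r between any two visits, two-sided 0.05 (the plan gives no sidedness). The plan reports no figure for the model itself, so there is none to reproduce.

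**Step 1: do the sentences fit together?**

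| Reading | Fits | Conflicts with |
|---|---|---|
| One model over four visits, time + group | the fixed- and random-effects lists | separate fits per visit; the decline-less hypothesis; the closing sentence |
| A separate model at each visit, group only | the sentence on the fit | time as a four-level factor; the subject random effect, which one record per subject cannot separate from residual error |
| One model with group-by-time, change contrast | the hypothesis; the closing sentence | separate fits per visit; the term is not in the list |

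No reading satisfies every sentence.

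**Step 2: what the additive model estimates.** With balanced complete data and equal correlations, the group coefficient is the plain average of the four visit-specific differences.

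- Constant benefit of 0.40 postpartum: (0 + 0.40 + 0.40 + 0.40)/4 = 0.30. The shortfall is 0.10/0.40 = 25%.
- Fading benefit of 0.6, 0.4, 0.1: (0 + 0.6 + 0.4 + 0.1)/4 = 0.275, one number with the pattern lost.
- Arms differing by 0.30 at every visit, baseline included: (4 × 0.30)/4 = 0.30, although there is no differential change.

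A small simulation (60 data sets, 107 per arm, r = 0.5) of the first case gave 0.300 for the additive model. With the interaction added, it gave differences in change of 0.41, 0.39 and 0.38 at the three visits.

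**Step 3: which contrast, once the interaction is present.** Per-visit variance, in units of 2/n per arm:

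- adjusted for baseline: 1 − r²
- unadjusted difference at the visit: 1
- change from baseline: 2(1 − r)

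Power = Φ(0.4/√(V × 2/107) − 1.96), single visit, no clustering:

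| r (assumed) | Adjusted: V, power | Unadjusted: V, power | Change: V, power |
|---|---|---|---|
| 0.3 | 0.91, 87% | 1.00, 83% | 1.40, 70% |
| 0.5 | 0.75, 92% | 1.00, 83% | 1.00, 83% |
| 0.7 | 0.51, 98% | 1.00, 83% | 0.60, 96% |

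Worked for r = 0.3, adjusted: √(0.91 × 2/107) = 0.130; 0.4/0.130 = 3.07; Φ(3.07 − 1.96) = 0.87.

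At r = 0.3 adjustment lowers the variance by 35% against change (1 − 0.91/1.40) and by 9% against the unadjusted difference (1 − 0.91/1.00). For r between 0 and 1 it is below both, since 1 − r² < 1 and 1 − r² = (1 − r)(1 + r) < 2(1 − r).

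**The case against.** The best defence is that the list says what the fixed effects will include, not that it is complete. The pairwise comparisons, the decline-less hypothesis and the closing sentence all point to a group-by-time contrast, and a journal article may leave the full model formula to another document. That stands as far as intention goes. A reader might infer that the investigators chose a main-effects-only analysis, so that the result will certainly be biased toward zero and the hypothesis left untested. The documents do not support that: if the interaction is in the model that is run, both problems disappear. What remains is that the article did choose to print the factors and their levels, and the printed terms do not yield the printed comparison.

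A second tempting inference is that adding the interaction alone commits the trial to a change-from-baseline analysis, so that the gain from adjustment is the full 35% in variance, or 87% against 70% power. It does not. A time-by-group model also gives the plain difference at each visit, which suits the Hypotheses section, and against that contrast the gain at r = 0.3 is 9%, or 87% against 83%.

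Nor can the baseline correlation be called modest as a matter of fact. The article says only that PSQI items are affected differently before and after birth, and gives no correlation. Baseline as a response row is a valid method once the interaction is present, so not using it as a covariate is a loss of efficiency and not an error.

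**Conclusion.** The point holds as a mismatch between the printed model and the printed primary hypothesis. Followed literally, the model fixes differential change at zero and returns 0.30 SD for a true constant benefit of 0.40 SD. The 25% rests on the additive reading, complete data and an equal effect at all three postpartum visits; other patterns give other figures. The closing sentence makes an omitted term the likelier explanation, but it then contradicts the list, and the sentence placing the fit at every time point contradicts time as a factor. These sentences need to be reconciled because they govern the primary analysis.

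The case for baseline adjustment is one of efficiency. Its direction holds at any correlation between 0 and 1, but its size depends on an r that the documents do not give. The power figures ignore clustering and serve only to compare the contrasts.

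**What to change.** For each sleep-quality and depression outcome, fit one model to the postpartum visits at which that outcome is collected. For the PSQI, ISI, EPDS and DASS these are 6 weeks, 4 months and 10 months. The Time 5 list in the Procedure does not name the MAF or ESS, so a three-visit model should not be presumed for them.

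- Fixed effects: group, visit, group-by-visit and the baseline score. A four-visit model with a common baseline mean for both arms is equivalent for this purpose.
- Random effects: keep subject and include cluster, since clusters are what is randomised.
- Report the adjusted group difference at each postpartum visit.
- Remove the wording that places the fit separately at every time point, and reword the closing sentence to name the contrast used.
- Outcomes with no baseline, such as the sleep diaries, omit the covariate if they are analysed in the same way.

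The cost is a change of wording. The baseline questionnaires are already collected at Time 1, so no new data are needed.

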## Methods

### Study design

This study will be a cluster randomised controlled trial. Participants will be recruited from consecutive attendees at prenatal classes at the Royal Prince Alfred Hospital (RPAH), Sydney Australia. In addition, the study is being advertised in obstetrician’s offices, and through the Study Facebook Page. Hence we will also accept self-referrals from these sources or from recommendations from friends. Participants from the same prenatal class will be randomised as a group in order to avoid contamination effects. The minimum in a cluster will be 3 and the maximum per cluster will be 10. Any participants from a group where less than 3 people consent or more than 10 people consent will join the next randomised cluster. Additional participants will join the clusters formed by the participants from RPAH based on the date they are recruited.

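### The analysis model names a random effect for subjects but none for the randomised cluster, so its standard errors ignore the clustering for which the sample size was inflated

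*Protocol article*

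**What the plan says.** The Study design section of the protocol article is explicit: "This study will be a cluster randomised controlled trial". It gives the unit of allocation, "Participants from the same prenatal class will be randomised as a group in order to avoid contamination effects", and its size, "The minimum in a cluster will be 3 and the maximum per cluster will be 10". Under Randomisation, one sealed envelope, labelled by cluster number, allocates the whole cluster once its members have completed the baseline components.

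The Statistical considerations section carries clustering into the sample size. It says that "the cluster design increases the sample size requirement according to the following formula" and gives 1 + (m – 1) × ICC. The published ICCs it draws on are for a mood scale, where the source "found the median value to be 0.01 for the HADS (interquartile range [IQR] 0 to 0.032, range 0 to 0.840". The choice made, with the multiplier applied to the unadjusted sample, is: "We aim for an average group size of 6, and to be conservative took the mean for the ICC of 0.42, requiring 2.6 times the". The target is 107 per group, 214 in all.

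The Data analysis plan then sets out a linear mixed model with fixed effects for time (four points) and group. On random effects it says: "Random effects will include subjects to account for between-subject variation". The primary hypothesis is evaluated by uncorrected pairwise comparisons of estimated marginal means. It is worded as a smaller postpartum deterioration in sleep quality with the intervention than with control. The only other relevant statement, under Strengths, is a general commitment to the CONSORT extension for cluster trials, which specifies no model.

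**The concern.** A subject random effect accounts for repeated measurements on the same woman. It does nothing for correlation between different women in the same cluster. Here that correlation has two plausible sources: the women largely come from the same prenatal class, and those in the intervention arm attend the psychoeducational sessions after baseline. If it exists and the model omits it, the standard error of the group effect is too small, confidence intervals are too narrow and the test rejects too often.

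The article also contradicts itself. The sample size section pays for clustering, and the analysis section then tests as if there were none. This is not detail left to a separate analysis plan, because the article names the fixed effects, the random effects and the test.

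**Working it through.** **Inputs.** From the article: mean cluster size m = 6; 214 women; ICC 0.42 (planning value); published ICCs with median 0.01 and interquartile range 0 to 0.032; significance level 0.05. Assumptions made here: a two-sided test (the article does not state sidedness), equal arms, and the same clustering in both arms. An ICC of 0.10 is added for illustration only.

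**The plan's own figure.** 41 × 2.6 = 106.6, so 107 per group follows from the two stated factors. The stated formula with the stated inputs gives 1 + 5 × 0.42 = 3.1, however, not 2.6; 2.6 would need an ICC of 1.6/5 = 0.32. That discrepancy is a separate matter, so both multipliers are carried below.

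**Units randomised.** 214/6 = 35.7, about 36 clusters, leaving about 36 – 2 = 34 degrees of freedom for the group effect.

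**Group comparison at one visit.** With design effect DE = 1 + 5 × ICC, the true standard error is √DE times the one reported when clusters are ignored. Actual type I error = 2 × [1 – Φ(1.96/√DE)].

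| ICC | DE | √DE | Actual type I error |
|---|---|---|---|
| 0 | 1.00 | 1.00 | 5.0% |
| 0.01 (quoted median) | 1.05 | 1.02 | 5.6% |
| 0.032 (quoted upper quartile) | 1.16 | 1.08 | 6.9% |
| 0.10 (illustrative) | 1.50 | 1.22 | 11.0% |
| 0.32 (implied by 2.6) | 2.60 | 1.61 | 22.4% |
| 0.42 (planning value) | 3.10 | 1.76 | 26.6% |

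**Simulation of the model as written.** Settings: 18 clusters of 6 per arm, four visits, group-by-time means, subject random intercept only, 6,000 runs per setting. Half of the variance not due to cluster was assigned to stable differences between women (an assumption). Rejection rates at one visit were 5.2% to 5.4% at ICC 0, 5.3% to 6.1% at 0.01, 6.8% to 7.3% at 0.032, 11.2% to 11.8% at 0.10 and 27.1% to 27.5% at 0.42. A t-test on cluster means in the same data stayed between 4.6% and 5.5%.

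**Change from baseline.** A cluster effect that is constant over time cancels from a change score; one that varies by visit does not. At ICC 0.42 the remaining variance is 0.58. Half of it, 0.29, is residual within a woman. Let v be the cluster variance that varies by visit. The subject-only model sees roughly 0.29 + v per woman, while the true value is 0.29 + 6v.

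| Share of cluster effect varying by visit | v | Variance ratio | Type I error, formula | Type I error, simulation |
|---|---|---|---|---|
| None | 0 | 0.29/0.29 = 1.00 | 5.0% | 5.1% |
| Half | 0.21 | 1.55/0.50 = 3.10 | 26.6% | 27.0% |
| All | 0.42 | 2.81/0.71 = 3.96 | 32.5% | 33.5% |

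At ICC 0.032 the corresponding simulated rates are 5.1%, 6.5% and 8.2%.

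**The case against.** **The wording is not exclusive.** Saying that random effects will include subjects does not rule out a cluster term, the article commits to the CONSORT cluster extension, and a fuller analysis plan may exist. A reader might infer that the plan deliberately excludes clusters, and the text does not support that. What it supports is that subjects are the only random effect named, for the stated purpose of between-subject variation, and that nothing elsewhere supplies the missing term. A reporting guideline cited in general terms does not supply it. A colleague fitting the model from this section would leave clusters out.

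**The ICC may be small.** This stands. A reader might infer that the false-positive rate certainly exceeds 5%, or that it is 27%. Neither follows. At ICC 0, the quoted lower quartile, there is no inflation, and across the quoted interquartile range it reaches at most 6.9%. The 0.42 is described as a mean, taken to be conservative, but it equals the midpoint of the quoted range, (0 + 0.840)/2, and lies far above the quoted upper quartile. Against that, the authors found no ICC for their sleep measures, and they cannot plan on 0.42 for size and in effect on zero for the test.

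**The stated hypothesis concerns change.** This also stands in part: a constant cluster effect cancels. Because the sessions come after the baseline questionnaires, effects that emerge later are plausible. The section can also be read as comparing groups at each visit.

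**Clustering may be mainly in one arm.** Controls receive booklets and calls; no control group sessions are described, and women from other sources join clusters by recruitment date. If clustering arose only in the intervention arm, the variance factor would be (1 + DE)/2. At ICC 0.42 that is (1 + 3.1)/2 = 2.05 and a type I error of 17%; at 0.032 it is 1.08 and 5.9%. The inflation is smaller but does not vanish.

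**Conclusion.** The concern holds. As written, the model omits the unit of randomisation and contradicts the article's own sample size reasoning, so its standard errors are valid only if outcomes are uncorrelated within clusters or, for change from baseline, if cluster effects do not vary over time. Nothing in the article establishes either condition.

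The size is conditional. It is slight (at most about 2 percentage points at one visit) if the ICC lies in the quoted interquartile range. It is severe (about 27% in place of 5%) at the ICC the plan itself assumes, given equal clustering in both arms and either a comparison at one visit or a cluster effect of which about half varies by visit. For change from baseline at that ICC, the range runs from no inflation to about 34%. These figures rest on clusters of 6 and a two-sided test, and those for change also on the assumed variance split. The correction is needed whatever the ICC proves to be, because the primary test should not depend on its being zero.

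**What to change.** In the Data analysis plan, add a random intercept for the randomised cluster, with women nested in it, and a cluster-by-visit random term so that change and visit-specific contrasts are also covered. Cluster-robust or cluster-level inference would serve equally. Base the degrees of freedom on the number of clusters (about 36, hence about 34 for the group effect) with a small-sample method such as Kenward-Roger or Satterthwaite. Since only one arm has sessions, consider letting the cluster variance differ by arm.

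The cost in data is nil: the envelopes already identify each cluster, and the Trial status section reports recruitment still in progress. The model gains two variance terms. For a comparison at one visit, intervals widen by about 2% at ICC 0.01, 8% at 0.032 and 76% at 0.42. For change from baseline at 0.42, the range is from no widening to roughly double (√3.96 = 1.99). Using a t quantile on 34 degrees of freedom adds about 4% (2.03/1.96). The wider intervals show the precision the design actually has.
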